### Sample size estimation

Sample size and statistical power has not been possible to estimate, since the variance of the outcomes is not known for many of the gathered data. Screening of 500 patients is realistic based on judgement by clinicians in the involved departments (e.g., by amount of neonatal admissions and referrals to neuropediatric clinic) and recruitment to previous studies in Denmark. Number of patients with CP is estimated from the Danish CP registry, indicating an incidence of 20 new patients from each of the 4 participating centers in the last years, therefore 160 is realistic to include in follow-up study, as children with high risk of CP also can be included, and a high interest from families to participate is anticipated. Distribution of participants in cohort II is estimated to derive from the neonatal pathway in 2/3 and from the infant pathway in 1/3 of cases.

The sample size for the GO-PLAY intervention trial has been calculated to be able to detect a large clinical effect (Cohen’s *d* = 0.8) corresponding to a difference between groups for PDMS-2 of 8 units, with greater than 80% statistical power at a 2-sided level of significance of 5%, comparing GO-PLAY (+ Standard of Care) with standard of care. Anticipating a standard deviation of 10.0, 26 patients are required in each of the two groups of primary interest (GO-PLAY versus standard of care). Accounting for 15% dropout rate, an estimated sample size is *n* = 60; approximately 30 participants per group.

Strategies for achieving adequate participant enrolment to reach target sample size includes dissemination to neuropaediatricians, and neonatologists, advertising on websites, and encouragement to disseminate knowledge about the study at paediatric departments in Denmark.

#### Assessments

For overview of schedule of enrolment, interventions, and assessments see Table 2.

**Table 2 Tab2:** Flow diagram according to SPIRIT recommendations (Standard Protocol Items: Recommendations for Interventional Trials)

**Variable / characteristic**	**Screening**	**Enrolment visit**	**Allocation to cohort III and randomi-zation to GO-PLAY**	**6 months CA**	**12 months CA**	**18 months CA**	**24 months CA**	**Additional visit if** **GO-PLAY** **t = 0**	**Additional visit if** **GO-PLAY** **t = 6**
*Infant characteristic*									
Eligibility screening	x								
Allocation and randomization			x						
Length, weight, head circumference		x		x	x	x	x	x	x
Gestational age		x							
Apgar score		x							
Birth measurements		x							
*CP risk factors*									
Familial disposition CP		x							
Imaging with CT / MRI^a^		x							
Co-morbidities		x		x	x	x	x	x	x
Medication		x		x	x	x	x	x	x
Genomic testing		x							
*Outcome measures*									
HINE [8]		x			x	x	x	x	x
GMA (if below 5 months) at age 12–15 and 16 weeks [7]		x							
PDMS-2 [25]					x	x	x	x	x
AIMS [26]		x		x	x			x	x
HAI (if below 12 months) [9]^b^		x		x	x			x	x
GMFM-66 [27]							x	x	x
BSID-IV-cog [28]					x	x	x		
COPM by interview in intervention group [29]								x	x
PSS questionnaire [30]		x			x		x	x	x
DASS-21 questionnaire [31]		x			x		x	x	x
MPOC-SP&20 questionnaire [27]^c^							x		x
ASQ questionnaire [32]							x		
Clinical assessment of CP diagnosis		x		x	x	x	x		
GMFCS if CP				x	x	x	x		
Mini-MACS if CP							x		
*Intervention*									
GO-PLAY intervention								x	x

*Abbreviations:*
*AIMS* Alberta infant motor scale, *ASQ* ages and stages, *BSID-IV, cog* Bayley scale of infant and toddler development III, cognitive part, *CA* corrected age, *CP* cerebral palsy, *COPM* Canadian occupational performance measure, by interview, *GO-PLAY* Goal Oriented ParentaL supported home ActivitY program, *GMA* general movements assessment, *DASS-21* depression, anxiety, and stress scale-21, *GMFCS* gross motor function classification system, *GMFM-66* gross motor function measure, *GMFCS* gross motor function classification system, *HAI* hand assessment for infants, *HINE* Hammersmith infant neurological examination, *MACS* manual ability classification system, *MPOC-SP&20* measures of processes of care – service providers, *MRI* magnetic resonance imaging, *PDMS-2* Peabody developmental motor scale, *PSS* parental stress scale, *t* time point

^a ^Optional repeat MRI at 12 and 24 months. ^b^At enrolment screening-HAI will be used. At subsequent visits the full HAI assessment will be used. ^c^ If included in the GO-PLAY study

##### Cohort I

The participants will be screened based on medical history, chart review and interview with parents regarding whether they should be included in the CP-EDIT study cohort II.

##### Cohort II

Participants in this cohort will be assessed with the following: a) Clinical examination by a neuropaediatrician including neurological assessment with HINE [8]; b) Cerebral MRI, preferably without anaesthesia. The MRI scan may be optional if pre-existing CT or ultrasound has established the aetiology of CP; c) Motor tests consisting for children below five months of age of GMA [7], HAI [9] and Alberta infant motor scale (AIMS [26]) and for children from 5–12 months of HAI and AIMS.

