### Objectives

In the CP-EDIT cohort and in the GO-PLAY RCT a large dataset will be gathered. The focus is on eight areas related to implementation and perspectives of the families, and dissemination of data will be distributed in scientific publications according to the following areas:*MRI.* To evaluate MRI findings on early diagnostic MRI of participants in cohort II, who later will be categorized as either definite CP, high risk of CP, unclear or definitely not CP.*Genetics.* To evaluate genetic findings in early whole genome sequencing of participants in cohort III, which have definite CP or high risk of CP.*GMA implementation.* To assess the feasibility of applying The Prechtl Qualitative Assessment of General Movements in a multi-center Danish hospital setting.*Prediction of CP*. To determine the clinical utility of the MRI, HINE, HAI, and GMA to predict a confirmed diagnosis of CP at 24 months, in infants referred below 12 months of age.*GMA/HINE/MRI vs. HAI*. To compare diagnostic accuracy of sHAI and GMA/HINE/MRI*.**GO-PLAY.* To analyse the effect of the GO-PLAY intervention with early family-centred set-up for children with definite or high risk of CP. For 6 months these participants will receive regular follow-up in the home of the family with physiotherapist and occupational therapist will monitor and strengthen goal-based training.*Parents perspective on intervention.* To explore parents’ perspectives on barriers and facilitators involved in early intervention.*Parents perspective on early diagnosis.* To analyse interviews of parents’ perspectives of gains and concerns when having an early diagnosis of high risk of CP and how it affects parent-infant interaction.

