#### Methods

*MRI*. Prospective cohort study. Descriptive analysis of MRI findings in the participants related to allocated group and outcome CP at age 24 months.*Genetics*. Prospective cohort study. Descriptive analysis of genetic findings in the participants related to allocated group and outcome CP at age 24 months.*GMA implementation.* Process evaluation of GMA implementation. Focus on fidelity, acceptability, and contextual factors influencing the feasibility of GMA.*Prediction of CP*. Prospective cohort study developing a transparent multivariable prediction model for individual diagnosis and prognosis of CP. We hypothesize that the MRI, HINE and GMA will have predictive validity equivalent to guideline recommendations and that the HAI score will be an important additive predictor to support early diagnosis of unilateral CP.Diagnostic test accuracy study. The aim is to determine the diagnostic accuracy (of sHAI for CP detection by using the interim diagnosis based on the combined assessment with MRI, GMA and/or HINE as a composite reference standard. The accuracy of sHAI will be assessed by measures of the test’s ability to detect the presence of high risk of CP.*GO-PLAY*. The primary aim of this trial is to compare the effectiveness of the GO-PLAY intervention, relative to the present standard of care, on the early motor development after 6 months in children with a definite or possible diagnosis of CP. The secondary aim is to compare the effectiveness of the GO-PLAY intervention, relative to the present standard of care, on parents’ ability to manage stress and anxiety and perceptions of health care services.*Parents perspectives on intervention*. Qualitative study based on focus groups of parents’ perspectives on barriers and facilitators in early intervention 1–3 months after participating in an early intervention program*Parents perspectives on early diagnosis*. Qualitative study based on individual semi-structured interviews of parents of infants with a diagnosis of high risk of CP. Parents are selected by purposive sampling and interviews are conducted in the home of the family 2–4 months after diagnosis of high risk of CP.

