#### Primary and secondary outcome measures

*MRI.* Primary results are a description of MRI findings in children included in the CP-EDIT cohort II. The type of MRI findings will be analysed and related to history, presence and type of CP and age of the child. Secondary results are to analyse if cranial ultrasound and/or CT is correlated to MRI findings.*Genetics.* A complete overview of pathogenic/likely pathogenic variants identified in the CP-EDIT cohort III and thus providing an overview of the genetic findings in an unselected cohort of children with suspected CP in a clinical setting.*GMA implementation.* Fidelity outcomes: Multifaceted training packages provided: (a) number, (b) content, (c) physiotherapists´ perspectives on the utility of sessions. Proportion of high-risk infants screened with GMA. Interrater reliability between the GMA assessors. Acceptability outcomes: Number of GMA videos (a) sent by parents, (b) made by physiotherapists. Additionally, assessment of physiotherapists´ confidence in providing a GMA score. The contextual factors change during the implementation process, these will be continually examined through observations and if relevant interview with stakeholders.*Prediction of CP*. The primary outcome is a confirmed diagnosis of CP “yes vs. no” at age 24 months. For infants defined as definite CP or high risk of CP, diagnosis will be confirmed by a neuropaediatrician according to the SCPE criteria [33]. Key secondary outcome: Motor function will be classified according to the Gross Motor Function Classification System (GMFCS), categorized into five levels from walking without limitation (level I) to non-ambulatory function (levels IV and V) [34]. For infants defined as unclear or definitely not CP, medical records will be reviewed for diagnosis and walking ability at the age of 24 months.*Diagnostic test accuracy study*. Infants at risk of CP will be assessed with sHAI, a 6-item structured video recorded play session of 5 min of duration. The test is performed in the clinic and assessed by a certified HAI assessor. A combination of MRI, GMA and/or HINE will be applied as the gold standard i.e., the high risk of CP or CP diagnosis reference standard.*GO-PLAY*. Patients referred to CP-EDIT trial will be randomized to receive either GO-PLAY intervention or standard care plus assessments. The primary outcome is improvement in motor development evaluated by Peabody Developmental Motor Scale 2 (PDMS-2) from baseline (T0) to the end of intervention (endpoint T6, 6 months post baseline. Key secondary outcomes will be HAI when the child is ≤ 12 months at the end of intervention, AIMS, Gross Motor Function Measure (GMFM-66), Bayley Scale of Infant and Toddler development 4, cognitive part (BSID-4, cog) and parental well-being. Neither the families nor the therapists responsible for intervention are blinded to group allocation. All outcome assessors will be masked to group allocation. The therapists responsible for data collection at each assessment point are not involved in the intervention, are unbiased as to group allocation, and have no access to previous assessments.*Parents perspectives on intervention.* Data are analysed using thematic analysis. Results from this study may support clinicians in understanding the parent’s perspectives and customize early home-based intervention to address parents’ expectations, concerns and needs in the Danish health care system.*Parents perspectives on early diagnosis.* Data are analyzed using thematic analysis approach, supported by investigator triangulation [35]. Findings are expected to be presented as themes and subthemes. This study may help clinicians to support the parent-infant interaction and tailor counselling to address parents’ experiences, concerns, and needs.

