
#### Examination and intervention modalities

##### MRI

All included participants in cohort II with risk of CP (*n* = 300) will be offered MRI as quickly as possible or at term if premature. We expect that at least half of the children will have an existing diagnostic MRI scan or have been offered an MRI scan due to clinical indications. The rest of the included children will be referred to a diagnostic MRI scanning at 3 Tesla by the paediatricians in the CP-EDIT program. If the child is not able to cooperate for the duration of the scan, standard sedative, or general anaesthesia in accordance with regular MRI scan protocols of children will be used.

MRI scans will be described clinically by radiologists at the participating hospitals. The findings will be categorised according to SCPE criteria (Surveillance of Cerebral Palsy in Europe). In participants where ultrasound or CT scanning of the patients have already been performed as part of clinical follow-up, the results will be gathered, and additional MRI may be optional. Repeat MRI at ages 12 and 24 months will be optional for participants in cohort III as part of the complementary NIBS-CP project (NeuroImaging of Babies during natural Sleep to assess typical development and Cerebral Palsy), which may provide important biological information about myelination, microstructure, and connectivity of the white matter fibre tracts, as well as the metabolic profile, including markers of neuronal integrity and glial markers, of the brain tissue [36, 37].

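### MRI may be omitted where ultrasound or CT is already diagnostic, so the planned ultrasound/CT–MRI correlation is open to partial verification bias; the two exemption wordings also differ

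*Protocol article*

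**What the plan says.** The protocol article states when MRI need not be done in two places, with different conditions.

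- Assessments, Cohort II: "The MRI scan may be optional if pre-existing CT or ultrasound has established the aetiology of CP". The condition is a diagnostic ultrasound or CT result.
- Examination and intervention modalities, MRI: where ultrasound or CT scans "have already been performed as part of clinical follow-up, the results will be gathered, and additional MRI may be optional". The condition is that an earlier scan exists, whatever it showed.

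The MRI section also says that all of cohort II (n = 300) "will be offered MRI as quickly as possible or at term if premature". On existing scans it says "We expect that at least half of the children will have an existing diagnostic MRI scan", and the sentence goes on to count children who have only been offered one on clinical grounds.

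MRI is then used in three ways:

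- The primary result of the MRI area describes MRI findings in cohort II.
- Its secondary result is a comparison with the earlier imaging: "Secondary results are to analyse if cranial ultrasound and/or CT is correlated to MRI findings".
- MRI is a named predictor of later CP: "To determine the clinical utility of the MRI, HINE, HAI, and GMA to predict a confirmed diagnosis of CP at 24 months".

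**The concern.** Only children with both kinds of scan can enter a correlation of ultrasound/CT with MRI. Under the Cohort II wording, whether a child has the second scan depends on the result of the first. Children whose ultrasound or CT settled the matter are those most likely to have no MRI, and most of them would probably have been positive on both. Losing concordant positive pairs makes the two methods look less alike than they are.

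At stake are the ultrasound/CT–MRI comparison and, to a lesser extent, the lesion frequencies in the MRI description. A result biased in this way could be read as evidence that ultrasound or CT misses more than it does.

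The MRI section's wording leads elsewhere. If skipping is unrelated to the earlier result, the main loss is precision. Which situation applies cannot be told until the two sections agree.

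**Working it through.** The plan gives no figure to reproduce here: no skip rate, no accuracy of ultrasound/CT against MRI, and no lesion prevalence. All inputs below are therefore assumptions and the results are illustrations.

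**Formulas.** Let Se and Sp be the true sensitivity and specificity of ultrasound/CT against MRI. Let f+ and f− be the fractions of ultrasound/CT-positive and -negative children who get MRI, and let r = f+/f−. Among children with both scans:

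- apparent sensitivity = Se·r / (Se·r + 1 − Se)
- apparent specificity = Sp / (Sp + (1 − Sp)·r)

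If r = 1, both return the truth, so skipping unrelated to the result causes no bias. The Cohort II wording exempts only diagnostic results, which pushes r below 1.

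**Scenario A.** Prevalence 0.50, Sp 0.95, Se 0.50 or 0.70, f− = 1. For simplicity all 300 children have had ultrasound/CT. The pair in each cell is for Se 0.50 / 0.70.

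| MRI done in positives | Apparent sensitivity | Apparent specificity | Phi | MRI lesion share among scanned |
|---|---|---|---|---|
| 100% | 0.50 / 0.70 | 0.950 | 0.50 / 0.67 | 0.50 / 0.50 |
| 75% | 0.43 / 0.64 | 0.962 | 0.47 / 0.64 | 0.47 / 0.46 |
| 50% | 0.33 / 0.54 | 0.974 | 0.42 / 0.60 | 0.43 / 0.40 |
| 25% | 0.20 / 0.37 | 0.987 | 0.32 / 0.50 | 0.39 / 0.33 |
| 10% | 0.09 / 0.19 | 0.995 | 0.22 / 0.36 | 0.37 / 0.28 |

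Take the 50% row with Se 0.50. The expected counts are 37.5 (both positive), 75 (MRI positive only), 3.75 (ultrasound/CT positive only) and 142.5 (both negative). Sensitivity is 37.5/112.5 = 0.33, and the lesion share is 112.5/258.75 = 0.43.

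The share of ultrasound/CT-positive children with an MRI lesion is 37.5/41.25 = 0.91, the same as with full scanning. Findings conditional on the ultrasound/CT result are not distorted in this model.

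Sensitivity, specificity and phi do not depend on how many of the 300 have had ultrasound/CT. The lesion share does: it moves less if fewer have.

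**Scenario B.** Se 0.60, Sp 0.90, prevalence 0.50, f− = 0.9, and f+ = 0.6, 0.4 or 0.2. Apparent sensitivity is 0.50, 0.40 or 0.25; for example, 0.36/(0.36 + 0.36) = 0.50. Apparent specificity is 0.93, 0.95 or 0.98. The lesion share is 0.45, 0.41 or 0.37. The direction is the same as in A.

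**Correction, same 50% row of A.** Of the 300, 82.5 are ultrasound/CT-positive and 217.5 negative. Apply the observed conditional lesion rates to all of them:

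- positives: 82.5 × 37.5/41.25 = 75 with a lesion, 7.5 without
- negatives: 217.5 × 75/217.5 = 75 with a lesion, 142.5 without

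Sensitivity is 75/150 = 0.50 and specificity 142.5/150 = 0.95, so the truth is recovered. In the 10% row only 7.5 + 0.75 = 8.25 positives have MRI, so the corrected figure would be unbiased in principle but very imprecise.

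**Prediction, for scale.** Assume CP probabilities of 0.90, 0.70, 0.40 and 0.15 for MRI/ultrasound-CT results ++, +−, −+ and −−. If half the ultrasound/CT-positive children lack MRI, complete-case MRI sensitivity for CP moves from 0.83 to 0.79 (Se 0.50) or from 0.84 to 0.77 (Se 0.70).

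**The case against.** The case against is substantial. MRI is offered to the whole of cohort II, skipping is only permitted, and at least half are expected to have or to have been offered an MRI. The low scanning rates that drive the large numbers have no support in the document. The affected analysis is a secondary result in an area described as descriptive, and no ultrasound/CT sensitivity or specificity is planned. Under the MRI section's wider wording, skipping need not depend on the result at all. If negatives were then the ones left unscanned, r would exceed 1 and the bias would reverse.

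Most of this stands, and it limits the size and certainty of the point. It does not remove it. The expected share with an existing MRI is not split by ultrasound/CT result, so it sets no floor on scanning among positives. A correlation in children with both scans falls with sensitivity, as phi shows above, whether or not sensitivity is reported.

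A reader might infer more: that the prediction model also carries verification bias. The article does not support that. Verification bias needs a reference standard whose availability depends on the test. Here the reference is CP status at 24 months, obtained by clinical confirmation or record review whether or not MRI was done. MRI is then a predictor that may be missing selectively. The article does not state a complete-case analysis, and how missing predictors are handled may properly sit in an analysis plan that is not shown.

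A reader might also point out that the 3rd-step criteria accept ultrasound in places while the model names MRI. Entry and classification rules need not match the coding of a predictor, so this is not an error.

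**Conclusion.** The point holds for the ultrasound/CT–MRI comparison. Under the Cohort II wording it is subject to partial verification bias: a raw correlation and apparent ultrasound/CT sensitivity are biased downwards, apparent specificity goes up slightly, and the MRI lesion frequency among scanned children may be understated. The size cannot be fixed from the document. It is small if few children skip MRI and material if half or more of the ultrasound/CT-positive children do. This rests on the assumed accuracy and prevalence above and on skipping that follows the ultrasound/CT result.

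Separately, the two exemption wordings differ and must be reconciled, because the bias depends on which one governs.

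For CP prediction the conclusion is narrower: MRI may be missing non-randomly, with modest effect in the illustration. The documents support neither a claim of verification bias there nor one that bias is built in.

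**What to change.** 1. Reconcile the Cohort II and MRI sections into one statement of when MRI may be omitted. Which condition to adopt is for the sponsor and investigators.
2. For every cohort II child, record the ultrasound/CT result and, where MRI is not done, the reason. Report the number without MRI by ultrasound/CT result.
3. Present MRI findings conditional on the ultrasound/CT result. Base any overall agreement, sensitivity or specificity on a Begg-Greenes type correction using all cohort II children with ultrasound/CT, in place of a raw correlation in children with both scans.
4. In the prediction model, let any handling of missing MRI, such as imputation, use the recorded ultrasound/CT result.

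A pooled imaging predictor (MRI, otherwise CT/ultrasound) with a modality indicator is tempting but should not be used. If exempt children are all positive, the indicator absorbs them, and in a simple main-effects model the lesion effect again comes from children with MRI alone. Under the wider wording, ultrasound/CT-negative children without MRI would be coded lesion-free. On the Scenario B inputs, 0.20/(0.20 + 0.45) = 31% of them have an MRI lesion. It would also displace the stated hypothesis about MRI itself.

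The cost is wording, one or two data fields and a short analysis, with no added scans. The small downside is that the correction assumes MRI uptake depends only on the recorded ultrasound/CT result and needs enough positives with MRI. Recording that result in more than two categories would make the assumption easier to defend.
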